## Data collection, management and analysis

### Data collection methods and participant retention

#### *Survey*

As there are no survey instruments capturing the objectives and characteristics of this study, the research team developed a survey tool for this trial. Survey instrument development was theoretically informed by the following existing validated outcomes measures: self-restraint-Weinberger Adjustment Inventory and the Basic Empathy Scale (BES) (Weinberger & Schwartz, 1990); Attitude Toward Women Scale for Adolescents (AWSA) (Galambos et al., 1985); Couple Violence Scale (ACVS) (Foshee et al., 1992); Dating Self-Protection Against Rape Scale (DSPARS) (Moore & Waterman, 1999); VicHealth 2006 Community Attitudes to VAW Survey (Taylor & Mouzos, 2006); Bystander Attitude Scale-Revised (BAS-R) (McMahon et al., 2014).

The survey items address student knowledge, attitudes and behavioural intention. In designing the survey items, we have been mindful of the cognitive and developmental age of Year 9 students, as well as Tasmanian literacy rates, in which half of Tasmanian 15-year-olds fall short of Australia's proficient reading standard (Thomson et al., 2019). Therefore, the items consist of straightforward and familiar language.

Data collected from student surveys at baseline, immediate post- and at 6-month follow-up will be complemented with data collected from interviews, focus groups and fidelity sheets. Interviews will be conducted with up to 20 students across the six intervention schools and with up to five external stakeholders, such as Senior Social Workers and Regional Safeguarding Leads. Focus groups will be conducted with up to eight program facilitators from Laurel House and Women's Legal Services Tasmania, and with up to 16 school staff members from a cross-section of participating schools.

#### *Interview*

The interview schedule for students assesses their experience of the program, the impacts the program has had on them, including changes in knowledge and understanding, changes they would make to the program, and the value they perceive in the program for others their age. The interview schedule for external stakeholders focuses on their views of region-specific needs, of the program and Laurel House's position as a program facilitator. Focus groups with

Laurel House facilitators explore implementation of the program, including experiences of facilitating the program, and the co-design process with schools. This data will be collected in conjunction with fidelity sheets filled out by facilitators which will be used to track student attendance and engagement in the program. The focus group schedule for school staff covers perceptions of the value of the program, experience of the co-design process, the response to the program from parents and students and changes being made to school policies or practices because of the intervention.

### *Retention*

Participant retention will be promoted throughout the study using reminders and vouchers. Students will be sent up to three automated reminders per survey via REDCap email reminders asking them to complete follow-up surveys. Students who participate in the follow-up interview will be offered a \$30 gift card to acknowledge their time. The structured school environment in which the program and follow-up will take place will also serve as a mechanism to keep participants engaged throughout the study.

If participants express a desire to discontinue or deviate from intervention protocols, the following data will be collected: reason for discontinuation or deviation; the type of deviation; when the deviation occurred; engagement in any alternative programs of a similar nature and the details of these programs; changes in knowledge, attitudes and behaviour intentions; and buy-in and acceptability of the program. Participants will be encouraged to continue with surveys to assess the impact of deviation or discontinuation, though they will not be obligated to provide this data.

## **Data management**

Only personal data necessary to the outcomes of the overall study will be collected. To ensure confidentiality of participant identities, all data will be securely stored on the La Trobe Research DataSpace (RDS). Identifiable data such as interview, focus group and fidelity sheets will also be held on the project's RDS and labelled with a code that does not link to participant identities. Nonidentifiable survey data will be held on REDCap and the RDS. The REDCap database does not link participant email addresses to their survey responses. Any data that is exported to the statistical analysis platform SPSS will be done in a way that ensures data is de-identified and has user privileges restricted to avoid the improper use of sensitive data. The RDS is accessed via password-protected desktops. Files containing sensitive information will be held in a restricted access folder on the RDS. At the end of the study, LTU researchers will retain materials for seven years after participants have turned 18, in line with the sponsor's archiving policies for health data. After this period, all trial-related items will be destroyed by LTU researchers. The Department of Social Services will separately retain quantitative data from the study indefinitely on their secure database. A Confidentiality Agreement will be drafted with the transcription service to protect sensitive information from being disclosed to unauthorised persons and to ensure researchers and transcribers comply with privacy laws and regulations.

The Data Management Committee will manage and monitor data, assessing safety and quality (See proposed ToR-Appendix O1).

## Statistical methods-analysis and missing data

The study results will be reported using the CONSORT guidelines for cluster RCTs. The proportion of students completing baseline, immediate-post and six-month follow-up surveys will be reported. A descriptive analysis will be used to summarise and describe the baseline characteristics (categorical or continuous variables) of the student participants, such as age, gender, sexual orientation, Indigeneity, country of birth, language spoken at home, and autism, ADHD or learning disabilities. For the quantitative outcome measures, a comparison of the intervention and control will be undertaken using SPSS or STATA to determine whether the Group 1 (treatment) mean ( $\mu_1$ ) is greater than the Group 2 (control) mean ( $\mu_2$ ) ( $H_0: \delta \leq 0$  versus  $H_1: \delta > 0$ ,  $\delta = \mu_1 - \mu_2$ ) on the primary outcome of knowledge. This will be repeated for secondary outcomes e.g. attitudes and behavioural intentions. Mean differences on outcomes will be assessed across trial arm and between baseline and post, baseline and follow up and post and follow up. The comparison will be made using a one-sided t-test (alpha 0.025) with the degrees of freedom based on the total number of subjects. Estimates for differences between intervention and control (odds ratios and least squares mean differences) will be adjusted for clustering (students nested within schools) and presented alongside 95% CIs. Intention to treat analysis will be completed and any missing data will be reported and managed using listwise deletion.

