| Program materials
Full-time educators,
Part-time practice champion
Regular internal and external supervision
Partnership with Women's Legal Service Tasmania
Evidence-based practice
Laurel House expertise and readiness
School buy-in and readiness
Crisis and counselling support
In-kind funding
Funding from Department of Social Services (DSS) | Resource development
Co-design with schools
Program adaptation
Educational session with school staff
Educational session with parents/carers
Educational sessions with students
School Student Champions
Management of disclosures by students, parents or school staff
Post-program reflection and revision
Managing key stakeholder relationships | Consistent student attendance and engagement at workshops
Teachers are upskilled and confident to take messages forward beyond program
Attendance and engagement of teachers and parents/carers at educational sessions
Increased knowledge and awareness among students about consent and the law; porn literacy; the gendered drivers of sexual violence; and how to access support services. | Adoption of respectful and consensual behaviours in relationships
Positive attitude shifts in relation to myths about sexual violence and gender stereotypes
Increased disclosures by victim-survivors
Improved student skills in relation to bystander techniques and understanding consent
Increased referrals to specialist services | Promote change to the school's socioecology on an individual, relational, and community level to address the drivers of sexual violence
Better informed and responsive parents and carers
Advance the evidence-base for primary prevention interventions in school settings |

**Figure 1:** Schools Education Program logic model

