## Outcomes

The primary outcome for this trial is:

- Improvements in students' **knowledge** about gender equality and sexual violence including consent, healthy relationships, and rape myths

The secondary outcomes are:

- Improvements in students' **attitudes** toward gender equality, rape myths, and empathy
- Improvements in students' **behavioural intentions** associated with consent and bystander intervention
- **Implementation outcomes**- fidelity, reach and retention, acceptability, sustainability.

The primary and secondary outcomes are measured using self-reported changes to students' knowledge from a 22-item scale developed for this study. This scale is theoretically underpinned by existing validated outcomes measures (detailed below) from studies on gender-based violence, general violence, or sexual violence. The items have been modified to simplify the language and/or to ensure the questions are appropriate for Year 9 students. Changes in mean scores will be analysed from baseline to immediate post intervention, then six months post and across trial arm.

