## Participant timeline

[figure not shown]

**Figure 2:** Study flow chart

All students will complete a baseline survey before randomisation, immediately-post intervention, and again at 6-month follow-up. A baseline survey will be completed by students before the commencement of the program in schools. An immediate-post survey and later a 6-month follow-up survey will also be administered. Students will complete the surveys in their own time online through REDCap, and each survey will be open for one

week. Students whose parents/caregivers have consented to their participation will be provided with a Participant Information and Consent Form (PICF) beforehand explaining the purpose of the research and its attendant risks and benefits, as well as the secure and confidential handling of their data. Students who consent to participate will receive a baseline survey which will collect data on demographic and potential confounder variables, as well as hypothesised outcome variables. Immediate-post surveys will contain the same hypothesised outcome variables. Six-month follow-up surveys will contain an additional item intended to collect self-reported data on which program sessions the students found most impactful.

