## Sample size

A parallel, two-group cluster-randomized design will be used to test whether the Group 1 (Intervention) knowledge average level ( $\mu_1$ ) is greater than the Group 2 (control) average level ( $\mu_2$ ) ( $H_0: \delta \leq 0$  versus  $H_1: \delta > 0$ ,  $\delta = \mu_1 - \mu_2$ ). Based on similar school-based dating violence prevention interventions in the USA (Lee & Wong, 2020), the assumed effect size for the primary outcome (knowledge) is 0.566, corresponding to a standardised mean difference (SMD) of 0.566. To detect this mean difference with 80% power, 6 clusters will be assigned to Group 1 and 6 to Group 2. The required average sample size per cluster is 12 for both groups, yielding a total of 72 subjects per group. Sample size calculations were performed using PASS 2024 (version 24.0.1).

The comparison will be conducted using a one-sided t-test, with degrees of freedom based on the total number of subjects and a Type I error ( $\alpha$ ) of 0.025. Assumptions include a common subject-to-subject standard deviation of 1, an intra-cluster correlation coefficient of 0.026, and a coefficient of variation for cluster sizes of 0.70926. To account for an estimated student dropout rate of approximately 20%, the required average sample size per cluster is increased to 15, resulting in a total of 180 students.

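### The trial is sized for one comparison of knowledge, but no primary time point is named and three wave pairs share one 0.025 rule with no order among them

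*Protocol*

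**What the plan says.** Protocol, Outcomes, defines the primary outcome as improvement in "knowledge about gender equality and sexual violence including consent, healthy relationships, and rape myths". It attaches no time point, and neither do the registry data set or the Objectives. The same section continues: "Changes in mean scores will be analysed from baseline to immediate post intervention, then six months post and across trial arm".

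Protocol, Participant timeline, sets three surveys: "All students will complete a baseline survey before randomisation, immediately-post intervention, and again at 6-month follow-up".

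Protocol, Sample size, plans one test of two arm means, with no wave named: "The comparison will be conducted using a one-sided t-test, with degrees of freedom based on the total number of subjects". It takes a standardised difference of 0.566, and "Assumptions include a common subject-to-subject standard deviation of 1".

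Protocol, Statistical methods-analysis and missing data, states one hypothesis on knowledge and then adds: "Mean differences on outcomes will be assessed across trial arm and between baseline and post, baseline and follow up and post and follow up". The test rule follows: "The comparison will be made using a one-sided t-test (alpha 0.025) with the degrees of freedom based on the total number of subjects". Estimates are to be adjusted for clustering. The section gives no primary wave, no testing order and no division of alpha, and does not mention the baseline knowledge score as a covariate.

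**The concern.** The contrast that decides the trial is part of the definition of the primary outcome, and the sample size rests on it. It is therefore a matter for the protocol and not a detail to leave to a statistical analysis plan. Here the sample size assumes one contrast and the analysis section lists three wave pairs under one significance rule. A team following the text could find a positive result at one wave and a null result at another, and nothing written beforehand would say which result answers the primary objective.

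The choice also affects power. The planned standard deviation of 1 describes a comparison of scores at one survey. A change score has a different standard deviation, which depends on a correlation the protocol does not give.

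**Working it through.** **1. The planned sample size reproduces.** Inputs from Sample size: difference 0.566, SD 1, ICC 0.026, CV of cluster size 0.70926, 6 schools per arm, 12 students per school, one-sided alpha 0.025, degrees of freedom from subjects (144 − 2 = 142).

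- Equal-cluster design effect: 1 + 11 × 0.026 = 1.286.
- L = m × ICC / (m × ICC + 1 − ICC) = 0.312 / 1.286 = 0.2426.
- Design effect with unequal clusters: 1.286 / [1 − CV² × L(1 − L)] = 1.286 / [1 − 0.5030 × 0.1837] = 1.417.
- SE = √(2 × 1.417 / 72) = 0.198, and 0.566 / 0.198 gives a noncentrality of about 2.85.
- Noncentral t power: 0.809 at 12 per school and 0.784 at 11. Twelve is the smallest sufficient size, as stated.
- Dropout: 144 / 0.8 = 180, as stated.

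The plan's figures are thus right for **one** comparison at **one** survey that makes no use of baseline.

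**2. Error rate if any one contrast counted as success.** Each wave pair is read as a between-arm difference in change, tested at one-sided 0.025. With equal correlations between waves, the three contrasts have mutual correlations 0.5, 0.5 and −0.5, whatever the common r. Simulation used 2,000,000 draws under the null.

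| What could count as success | One-sided error |
|---|---|
| One named contrast | 0.025 |
| Two changes from baseline | 0.045 |
| Post and follow-up means instead of changes, r = 0.3 / 0.5 / 0.7 | 0.048 / 0.045 / 0.042 |
| All three wave pairs, equal wave correlations | 0.066 |
| All three, correlations 0.6 (adjacent waves) and 0.4 (baseline to follow-up) | 0.062 |
| All three if independent, 1 − 0.975³ | 0.073 |
| Bonferroni bound, 3 × 0.025 | 0.075 |

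The third row shows that the inflation does not depend on reading the contrasts as change scores.

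**3. The post-to-follow-up contrast.** If the programme raises knowledge by δ at both surveys, the between-arm difference in post-to-follow-up change is δ − δ = 0. The contrast then has only its false-positive rate. If the effect fades, its expected value is negative.

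**4. Power by choice of contrast.** Let r be the baseline-to-post correlation. The protocol gives no value, so a range is assumed, with the same r at school and student level. The variance factor relative to a post-only comparison is 2(1 − r) for a change score and 1 − r² with the baseline score as covariate. Degrees of freedom are the protocol's own: 142, less one for the covariate.

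| r | Change-score factor | Power | Covariate factor | Power | Post-only power |
|---|---|---|---|---|---|
| 0.3 | 1.40 | 0.67 | 0.91 | 0.84 | 0.81 |
| 0.5 | 1.00 | 0.81 | 0.75 | 0.91 | 0.81 |
| 0.6 | 0.80 | 0.89 | 0.64 | 0.94 | 0.81 |

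The change-score factor exceeds 1 only when r is below 0.5. The ratio of the two factors is 2(1 − r) / [(1 − r)(1 + r)] = 2 / (1 + r), which exceeds 1 for every r below 1. The covariate is therefore always the more efficient use of the baseline survey.

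**The case against.** The strongest reply is that the protocol commits to no multiple testing. It states one hypothesis on knowledge, speaks of the comparison in the singular, and says only that differences between waves will be assessed. A reader might infer that each contrast is tested at 0.025 and that any positive one wins, so that the trial's error rate is 6.6%. The text does not say this. That figure also requires a post-to-follow-up gain to be accepted as a primary success, which is stated nowhere. This part of the reply stands: 4.5% to 6.6% describes what the text permits. It does not remove the gap, because no sentence identifies the deciding contrast.

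A reader might also infer that the baseline survey is wasted, or that the planned analysis loses power. The documents do not support that. A change score uses baseline, and loses to a post-only comparison only if r is below 0.5, which is unknown. Nor does the protocol clearly commit to change scores.

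Leaving the baseline score off a covariate list is not an error in itself. The analysis plan may supply it, and the baseline survey is said to collect potential confounders. Baseline adjustment is therefore an efficiency recommendation that accompanies the fix.

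Finally, power computed with 10 cluster-based degrees of freedom looks worse: 0.73 for post-only. That loss comes entirely from the degrees of freedom. It is a separate question and should not be charged to the choice of contrast.

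**Conclusion.** The point holds in this form: the protocol powers one comparison of knowledge, names no primary time point, and lists three wave pairs under a single one-sided 0.025 rule without order or allocation of alpha. If any one positive contrast were accepted, the one-sided error would be about 4.5% with the two baseline contrasts and about 6.6% with all three. The second figure is about 2.6 times the planned 2.5%, and it cannot exceed 7.5%. These figures assume between-arm contrasts, approximate normality and, for the 6.6%, equal correlations between waves.

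On power, the documents support only a conditional statement. A change score is worse than post-only below r = 0.5, equal at 0.5 and better above it. Baseline adjustment is better than a change score at every r below 1.

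**What to change.** Name one primary contrast in Outcomes, Sample size and Statistical methods. For example: the between-arm difference in knowledge at the immediate-post survey, from the cluster-adjusted model, one-sided 0.025 with a 95% CI, with the student's baseline knowledge score as a covariate. The logic model (Figure 1) offers some support for that wave, since it lists "Increased knowledge and awareness among students about consent and the law" among the short-term outcomes. It gives no date, however, and the choice of wave is the sponsor's. Test the other wave only if the primary is positive, and report post-to-follow-up change descriptively.

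This ordering is cheaper than splitting alpha. At the planned size, post-only power per contrast would be about 0.72 with two contrasts at 0.0125 each, and about 0.67 with three at 0.0083 each.

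The cost is mainly wording. The baseline survey is already planned before randomisation, and the data set section reports that recruitment has not begun. There are two downsides:

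- The other wave no longer counts as a primary success on its own.
- Student-level baseline adjustment needs each student's surveys linked. Data management and Confidentiality say that REDCap does not tie email addresses to responses, and they describe no study code for the surveys. Confirm that such a code exists. A student-level change score needs the same link; without it, a baseline-to-post contrast behaves as if r were near 0 (variance factor 2), with power of about 0.52.

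### The power calculation and the primary test take degrees of freedom from 144 students instead of 12 randomised schools: the stated 80% power is about 73%, and the one-sided 2.5% error rate is exceeded.

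*Protocol*

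**What the plan says.** The Trial design section makes the school the unit of randomisation. The Sample size section fixes the numbers: "To detect this mean difference with 80% power, 6 clusters will be assigned to Group 1 and 6 to Group 2", and "The required average sample size per cluster is 12 for both groups, yielding a total of 72 subjects per group". Its inputs are an effect "corresponding to a standardised mean difference (SMD) of 0.566", "a common subject-to-subject standard deviation of 1", and "an intra-cluster correlation coefficient of 0.026, and a coefficient of variation for cluster sizes of 0.70926", with a one-sided type I error of 0.025. It names the test: "The comparison will be conducted using a one-sided t-test, with degrees of freedom based on the total number of subjects".

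The section Statistical methods-analysis and missing data carries the same rule into the analysis: "The comparison will be made using a one-sided t-test (alpha 0.025) with the degrees of freedom based on the total number of subjects". It applies the comparison to the secondary outcomes as well. The next sentence says that the estimated differences will be adjusted for students being nested in schools and shown with 95% CIs. No small-sample or cluster-based df is given anywhere.

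**The concern.** The treatment effect is estimated from 12 independent units. The design effect enlarges the variance to allow for similarity within schools. It does not allow for the fact that the between-school part of that variance is itself estimated from only 12 schools. That second uncertainty enters through the df, and the Protocol sets these as if students had been randomised.

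Two things are at stake. The planned power is not a property of the design. And a result with a t statistic between 1.98 and 2.23 would be declared significant without meeting the 0.025 level that the trial claims.

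The analysis text also leaves an ambiguity. It names a t-test with subject-based df, then says that the estimates are adjusted for clustering. It does not say that the test and the interval come from the same model. If they do not, the p-value and the CI for one effect could disagree.

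**Working it through.** **Inputs (all from Sample size, except the unit of randomisation, from Trial design).** SMD d = 0.566, SD = 1, ICC = 0.026, CV of cluster size = 0.70926, K = 6 schools per arm, m = 12 analysed students per school (72 per arm, 144 in total), one-sided alpha = 0.025, 20% dropout.

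**Design effect (DE).** Two standard forms for unequal clusters were used, because the Protocol does not say which one its software applied.
- (a) DE = 1 + ((1 + CV²)m - 1) × ICC = 1 + (1.50305 × 12 - 1) × 0.026 = 1.443.
- (b) Relative efficiency: DE = [1 + (m - 1) × ICC] / [1 - CV² × L(1 - L)], with L = m × ICC / [1 + (m - 1) × ICC] = 0.312/1.286 = 0.2426. This gives 1.286 × 1.102 = 1.417.

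**Standard error and noncentrality.** SE = sqrt(2 × DE/72); noncentrality = 0.566/SE.
- (a) SE = 0.200, noncentrality 2.827.
- (b) SE = 0.198, noncentrality 2.853.

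**Power from the noncentral t distribution.**

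| Completers per school | df | Critical value | Power (a) | Power (b) |
|---|---|---|---|---|
| 11 | 130 (subjects) | t(130) | 77.8% | 78.4% |
| 12 | 142 (subjects) | 1.977 | 80.2% | 80.9% |
| 12 | 10 (schools) | 2.228 | 72.2% | 73.0% |
| 15 (no dropout) | 10 | 2.228 | 78.2% | 79.2% |
| 16 | 10 | 2.228 | 79.8% | 80.9% |
| 17 | 10 | 2.228 | 81.2% | 82.4% |

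The first two rows reproduce the plan: with subject df, 12 is the smallest average school size that reaches 80%. The dropout step also reproduces: 12/0.8 = 15 per school, and 15 × 12 = 180. So the stated 80% rests on the subject-based df.

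**What 80% would need with cluster df.** With six schools per arm, 16 completers under (b) or 17 under (a). Enrolment is 16/0.8 = 20 per school (240 in total), or 17/0.8 = 21.25, rounded up to 22 (264 in total). With 12 completers per school, seven schools per arm (12 df) give 80.0% to 80.7%.

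**Type I error (nominal 0.025).** If the statistic follows t on 10 df, P(t > 1.977) = 0.038. Null simulations (20,000 to 40,000 trials, unequal school sizes) at the planned ICC gave:

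| Analysis | Reference df | One-sided error |
|---|---|---|
| Random-intercept or equivalent weighted model | subjects | 0.029 to 0.030 |
| t-test on school means | subjects | 0.036 |
| t-test on school means | 10 | 0.024 |
| Pooled t-test that ignores clustering | subjects | 0.047 to 0.050 |
| Cluster-robust standard errors | subjects | 0.057 to 0.058 |

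At an assumed ICC of 0.10 (not in the Protocol, used only to show the range), the pooled t-test reaches about 0.11 and the weighted model 0.039.

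**The case against.** The best defence is that nothing is miscalculated. The design effect includes both the ICC and the cluster-size variation, the Protocol states its choice of df openly, and its figures reproduce. The analysis text also promises adjustment for clustering. The natural reading is then a mixed model with subject df, for which the type I error at the planned ICC is only about 0.03. The larger figures need a pooled t-test, cluster-robust standard errors or a higher ICC, none of which the Protocol names.

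Further, 10 df is a convention. At an ICC of 0.026 a Satterthwaite-type df varies widely from one data set to the next and can lie well above 10. A mixed model read against exactly 10 df was somewhat conservative in simulation (0.018).

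Much of this stands as a limit on size. The fault is the choice of reference distribution, not a slip in the sums. The excess error may be as small as half a percentage point, and the possible conflict between p-value and CI is an ambiguity, not a demonstrated contradiction. None of it supports subject-based df: every subject-df analysis tried exceeded 0.025. Nor can a separate SAP settle the matter, because the Protocol itself fixes the df and an SAP with cluster df would contradict it.

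**Conclusion.** The concern holds. With the Protocol's own inputs, and df based on the 12 schools, power at 12 completers per school is 72.2% to 73.0%, not 80%. Even with no dropout it stays just below 80%. The one-sided error rate exceeds 0.025: 0.038 in the t(10) reference case, and between about 0.03 and 0.06 at the planned ICC, depending on the analysis model. The power figures rest on the stated SMD, ICC and CV, on the usual noncentral t approximation, and on 10 df as the conventional reference. This affects the primary confirmatory test and the stated justification of the sample size, so it should be corrected before recruitment starts.

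**What to change.** - In Sample size and in Statistical methods-analysis and missing data, replace the subject-based df with cluster-based df.
- Name one analysis, and take both the p-value and the 95% CI from it. This can be a linear mixed model with a random school intercept, REML and Kenward-Roger or Satterthwaite df, or a weighted school-level t-test with 10 df. The weighting matters with school sizes this uneven: an unweighted t-test on school means with 10 df had only about 60% simulated power.
- Restate the power at 12 completers per school as about 72% to 73%. Alternatively, raise the target to 16 to 17 completers per school (240 to 264 enrolled). The Recruitment section reports about 900 students in the 12 interested schools.
- Adjusting for the baseline score would recover much of the loss. With an assumed pre-post correlation of 0.4, which the Protocol does not give, the variance is multiplied by 1 - 0.4² = 0.84 and power at 10 df becomes 79.4% to 80.1%. A higher correlation would give more.

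The cost is wording in two sections, one rerun of the sample size software with cluster-based df, and a less favourable power statement. The restatement alone needs no extra students.

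### Listwise deletion is paired with an intention-to-treat claim: students with a missing analysed survey are dropped, the scope of deletion is undefined, and the sample-size inflation gives no protection against bias

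*Protocol*

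**What the plan says.** The missing-data rule is one sentence in the protocol, Statistical methods-analysis and missing data: "Intention to treat analysis will be completed and any missing data will be reported and managed using listwise deletion". No alternative method and no sensitivity analysis is named.

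The same section lists several contrasts: "Mean differences on outcomes will be assessed across trial arm and between baseline and post, baseline and follow up and post and follow up". The test is also fixed there: "The comparison will be made using a one-sided t-test (alpha 0.025) with the degrees of freedom based on the total number of subjects". Estimates are to be adjusted for clustering; adjustment for the baseline score is not mentioned.

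The Participant timeline sets three waves: "All students will complete a baseline survey before randomisation, immediately-post intervention, and again at 6-month follow-up". On how they are completed it says: "Students will complete the surveys in their own time online through REDCap, and each survey will be open for one" week.

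The Sample size section raises the average per school from 12 to 15, and so the total from 144 to 180: "To account for an estimated student dropout rate of approximately 20" per cent.

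The section on Assignment of intervention states that everyone is unblinded once baseline forms are complete.

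**The concern.** Listwise deletion removes any student who lacks a value that the analysis needs. Students who remain can still be grouped by their school's allocation, but the set is selected by response after randomisation. A reader of the trial report may take intention to treat to mean that all enrolled students are included, and they will not be.

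Three things are at stake:

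- **Scope.** If deletion runs across all three waves, a student who missed only the 6-month survey is also lost from the immediate-post comparison.
- **Precision.** Surveys that were answered are thrown away.
- **Bias.** Surveys are voluntary, done in students' own time, and follow unblinding, and only intervention schools receive the program during the trial. Loss could plausibly depend on earlier scores and differ by arm. Enrolling more students does not correct that.

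**Working it through.** **1. Reproduce the plan's figure.** Inputs, all from the Sample size section: "the assumed effect size for the primary outcome (knowledge) is 0.566"; "Assumptions include a common subject-to-subject standard deviation of 1"; ICC 0.026; CV of cluster size 0.70926; one-sided alpha 0.025; 6 schools per arm; 12 analysed students per school.

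- Individually randomised size: 2 × (1.960 + 0.842)² / 0.566² = 49.0, rounded up to 50 per arm.
- Design effect at m = 12: 1 + [(1 + CV²)m − 1] × ICC = 1 + (1.503 × 12 − 1) × 0.026 = 1.443.
- 50 × 1.443 = 72.1 per arm, against 72 stated.
- Standard error: √(2 × 1.443 / 72) = 0.200. Noncentrality: 0.566 / 0.200 = 2.83. Power on 142 degrees of freedom: 80.2%.
- Inflation: 144 / 0.8 = 180.

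The plan's figure reproduces.

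**2. Power with fewer complete students.** Same formula, with the protocol's subject-level degrees of freedom and the CV held fixed:

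| Complete of 180 | Lost | Per school | Power |
|---|---|---|---|
| 180 | 0% | 15 | 85.6% |
| 144 | 20% | 12 | 80.2% |
| 126 | 30% | 10.5 | 76.4% |
| 115 | 36% | 9.6 | 73.7% |
| 108 | 40% | 9 | 71.6% |
| 90 | 50% | 7.5 | 65.5% |

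The 115 row assumes that 20% miss each follow-up independently and that deletion spans all waves: 0.8 × 0.8 = 0.64, and 0.64 × 180 = 115.2. Under that assumption 2 × 0.2 × 0.8 = 32%, about 58 students, have exactly one follow-up survey and would be discarded. If deletion is per comparison, baseline-to-post and baseline-to-6-months each keep 144, and only post-to-6-months falls to 115.

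**3. Bias when loss depends on baseline.** Assumptions not in the protocol: correlation r = 0.5 between waves; 20% loss in the intervention arm, greater among low scorers, with an odds ratio of 2 to 3 per SD of baseline; loss at random in the control arm. Completers' baseline mean in the intervention arm then rises by about 0.13 SD (odds ratio 2) to 0.18 SD (odds ratio 3).

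- Unadjusted post score: bias = r × shift = +0.06 to +0.09 SD.
- Change score: bias = (r − 1) × shift = −0.06 to −0.09 SD.
- Baseline-adjusted: about zero.

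If the selective loss is in the control arm instead, the signs reverse.

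**4. Bias when 6-month loss depends on the post score.** Large-sample simulation, ignoring clustering. True difference 0.566; assumed correlations 0.5 (baseline with post, and with 6 months) and 0.6 (post with 6 months); logistic loss with slope 1 per SD, about 20% overall. Estimated 6-month differences:

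| Loss depends on | Complete case | Complete case, baseline-adjusted | Using baseline and post of all students |
|---|---|---|---|
| Nothing | 0.572 | 0.571 | 0.570 |
| Baseline, intervention arm only | 0.651 | 0.561 | 0.563 |
| Post score, both arms | 0.531 | 0.544 | 0.567 |
| Post score, intervention arm only | 0.672 | 0.628 | 0.565 |

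In the third row the loss rates differ by arm (23.7% control, 15.8% intervention) because the intervention raises the post score. In the last two rows baseline adjustment is not enough, whereas using the observed post scores recovers the true value.

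**The case against.** Four points on the other side carry weight.

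- **Deletion across all waves is only one reading.** The protocol lists separate comparisons. If deletion is per comparison, a missed 6-month survey costs nothing in the baseline-to-post contrast. This stands: the fault is that the scope is undefined, not that the wider deletion is certain.
- **The planned loss is already paid for.** A reader might infer that listwise deletion leaves the trial underpowered as designed. The document does not support that: at a total loss of 20%, power is 80% by construction. Independence between waves is also a pessimistic assumption, since students who leave early tend to miss both follow-ups. The 115 figure is conditional.
- **The bias inputs are assumed.** A reader might infer that the effect will be inflated. The protocol gives no correlation and no pattern of loss. The Outcomes section refers to changes in mean scores, for which the baseline-dependent bias in the working points downward. With data missing completely at random there is none. The Retention section plans up to three reminders per survey, with no distinction by arm, and encourages students who discontinue to keep answering.
- **Intention to treat can simply mean analysis by allocated arm.** On that reading the sentence does not contradict itself, and completion at each wave will be reported. But the protocol does not define the term, and the set analysed remains complete cases.

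What survives is that the protocol itself chooses listwise deletion, so this is not detail left to a separate analysis plan, and a method that uses the discarded surveys is readily available.

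**Conclusion.** The point holds in a limited form. The protocol fixes a complete-case analysis beside an intention-to-treat claim and does not say how far deletion reaches.

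Power stays at about 80% for a total loss of 20%. It drops below that only with more incomplete records, to about 74% at 115 complete students under the stated assumptions.

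The more important weakness is bias, which is possible but not established: about 0.06 to 0.09 SD in either direction when loss in one arm depends on baseline. When 6-month loss depended on the post score, the estimate moved from 0.566 to between 0.53 and 0.67 in the scenarios tried, or 0.54 to 0.63 after baseline adjustment. These sizes rest on assumed correlations and loss models and show what could happen; they do not predict it.

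**What to change.** Replace listwise deletion with one likelihood-based linear mixed model for the baseline, post and 6-month scores. It should have arm-by-time terms with a common baseline mean, a random school effect, within-student correlation, and small-sample degrees of freedom suited to 12 schools. Include every enrolled student with at least one outcome value, analysed by the school's allocation, and say that this is what intention to treat means here. The model is valid if data are missing at random given the observed scores. Report the complete-case result as a sensitivity analysis, stating whether its deletion is per comparison or across waves, and add one analysis that allows for data not missing at random.

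The cost is a wording change and slightly more analysis work; SPSS and Stata, the packages named in the protocol, both fit such models. One practical check is needed. The Data management and Confidentiality sections say that email addresses are not linked to survey responses, so the sponsor should confirm that a study code links each student's surveys across waves. Within-student changes from baseline, and listwise deletion across waves, would need the same link. Recruitment had not begun at this version, so the change can be made before any outcome data exist.
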